## Abstract

**Background:**

Vagal nerve stimulation (VNS) can be indicated in patients with drug-resistant epilepsy, who are not eligible for resective epilepsy surgery. In VNS therapy, the responder rate (i.e., percentage of subjects experiencing ≥50% seizure reduction) is ~50%. At the moment, there is no widely-accepted possibility to predict VNS efficacy in a particular patient based on pre-implantation data, which can lead to unnecessary surgery and improper allocation of financial resources. The principal aim of PRediction of vagal nerve stimulation EfficaCy In drug-reSistant Epilepsy (PRECISE) study is to verify the predictability of VNS efficacy by analysis of pre-implantation routine electroencephalogram (EEG).

**Methods:**

PRECISE is designed as a prospective multicentric study in which patients indicated to VNS therapy will be recruited. Patients will be classified as predicted responders vs. predicted non-responders using pre-implantation EEG analyses. After the first and second year of the study, the real-life outcome (responder vs. non-responder) will be determined. The real-life outcome and predicted outcome will be compared in terms of accuracy, specificity, and sensitivity. In the meantime, the patients will be managed according to the best clinical practice to obtain the best therapeutic response. The primary endpoint will be the accuracy of the statistical model for prediction of response to VNS therapy in terms of responders and non-responders. The secondary endpoint will be the quantification of differences in EEG power spectra (Relative Mean Power, %) between real-life responders and real-life non-responders to VNS therapy in drug-resistant epilepsy and the sensitivity and specificity of the model.

**Discussion:**

PRECISE relies on the results of our previous work, through which we developed a statistical classifier for VNS response (responders vs. non-responders) based on differences in EEG power spectra dynamics (Pre-X-Stim).

**Trial Registration:**

www.ClinicalTrials.gov, identifier: NCT04935567.

## Introduction

### Background and Rationale

The main goal of epilepsy treatment is long-term seizure cessation. In two-thirds of patients, seizure-freedom can be established with antiseizure medication (ASM) intake (1). Seizures persist despite ASM treatment in one-third of patients, and these are labeled as drug-resistant or refractory epilepsy. Resective surgery should be considered in all drug-resistant cases. If the patient is not eligible for resection, neurostimulation can be indicated as a therapeutic option.

Vagal nerve stimulation (VNS) is the most commonly used neurostimulation method in the treatment of patients with epilepsy. More than 100,000 patients have already been implanted world-wide. The therapy with VNS provides a high chance for a substantial seizure reduction. Approximately 50% of implanted patients are responders (seizure reduction ≥50%) after 1 year of VNS, and about 5 % of implanted patients reach complete seizure freedom. However, there is a group of implanted patients, non-responders (seizure reduction <50%), who do not significantly benefit from VNS (2–5).

Currently, we are not able to reliably predict the response to VNS based on patients' pre-implantation data. This prediction is crucial for proper selection of VNS candidates, and reduction of unnecessary surgery and costs associated with the implantation. Moreover, the ability to predict VNS efficacy seems to be essential for VNS use in resource-limited countries.

Our group developed and validated a statistical model (Pre-X-Stim) for the prediction of VNS efficacy (6). This algorithm is based on the analysis of routine scalp electroencephalogram (EEG) data, which is the main advantage of our approach because it is an inexpensive, easily-accessible method with minimal burden on the patient. When summarizing the procedure in brief, we retrospectively identified pre-implantation routine scalp EEG recordings in patients treated with VNS for drug-resistant epilepsy. The patients were characterized as responders or non-responders based on the long-term outcomes. The EEG recordings were segmented into several time intervals. In each interval, the changes of dynamics in EEG power spectra were calculated. Based on these changes, the statistical classifier for a prediction of VNS efficacy was developed (Patent No. EP 3437692). The validity of the model was verified on an independent data set, in which it was able to predict the response to VNS with 86% accuracy, 83% sensitivity, and 90% specificity. The usability of this model with different EEG systems was subsequently proven (7). Our previous studies were, however, retrospective and monocentric, and these are the crucial limitations that we would like to overcome with the proposed project, PRECISE (PRediction of vagal nerve stimulation EfficaCy In drug-reSistant Epilepsy).

### Objectives

The study is designed to determine the availability of VNS prediction based on pre-implantation data. The main goal is to validate Pre-X-Stim in a real-life prospective study.

The primary aim of our study is to evaluate whether we are able to predict VNS efficacy in an individual patient based on the pre-implantation scalp EEG. We defined two hypotheses:

We hypothesize that there are differences in the dynamics of EEG power spectra in response to activation methods (eye-opening/closing, photic stimulation, hyperventilation) between responders and non-responders to VNS therapy.We hypothesize that we can predict the patient's response to VNS therapy in terms of responder vs. non-responder by our statistical model based on the changes in the dynamics of EEG power spectra.

Based on these hypotheses the primary and secondary endpoints were established. Primary endpoint involves the accuracy of the statistical model for prediction of response to VNS therapy in terms of responders and non-responders in drug-resistant epilepsy, evaluated after 2 years. Secondary endpoints include (1) the quantification of differences in EEG power spectra (Relative Mean Power, %) between real-life responders and real-life non-responders to VNS therapy in drug-resistant epilepsy; (2) prediction of patients' response to VNS therapy in terms of responders (≥50% seizure reduction from baseline) and non-responders (<50% seizure reduction from baseline). Each endpoint will be evaluated 2 years after recruitment.

### Trial Design

PRECISE is an investigator-initiated study. It is a prospective multicentric, multinational clinical study that will be started in January 2022. The patients with drug-resistant epilepsy will undergo standard VNS implantation based on a clinical decision. Before implantation, a scalp EEG, according to the study protocol, will be recorded. The EEG will be mathematically processed, and the patient's predicted outcome in terms of predicted responder vs. predicted non-responders will be statistically determined. The stimulation parameters and ASM therapy will be modified according to the best clinical practice. The real-life outcome will be measured by the percent of seizure reduction. Subsequently, the real-life and predicted outcomes will be compared in terms of accuracy, sensitivity, and specificity.

The proposed study is based on the results of our previous work, through which a statistical model was developed for the prediction of VNS efficacy based on a mathematical and statistical analysis of scalp EEG data (6).

## Methods and Analysis

### Study Setting

The PRECISE study has not yet been recruited. The study is planned to be initiated in nine European countries (Czech Republic, France, Germany, UK, Spain, Austria, Portugal, Italy, and Belgium) in 2022.

Brno Epilepsy Center, the coordinating center for the study, is responsible for education and training of research staff, tracking participants' enrolment, mathematical analysis, including statistics of scalp EEG, and reporting of the study.

The other collaboration centers are responsible for patient selection according to eligibility criteria, adherence to all criteria of the study as described below, and adjustment of ASM and VNS therapy according to the best clinical practice.

### Eligibility Criteria

Inclusion criteria include a diagnosis of drug-resistant epilepsy based on the definition of the International League against Epilepsy (8). The patient has to be indicated to VNS therapy based on a clinical decision.

All adult patients with drug-resistant epilepsy indicated to VNS will be screened in participating centers for inclusion criteria. Written informed consent for each study participant will be obtained prior to any data collection.

Inclusion criteria are as follows:

Drug-resistant epilepsy indicated to VNS based on clinical decision. Drug-resistant epilepsy is defined as a failure of adequate trials of two tolerated, appropriately chosen and used antiepileptic drug schedules (whether as monotherapy or in combination) to achieve sustained seizure freedom (8).Age ≥18 years.Availability to record 20 min EEG with photic stimulation, hyperventilation, and eye-opening/closing according to the pre-defined protocol.Availability of seizure diaries at least 3 months before VNS implantation OR reliable information about seizure frequency at least 3 months before VNS implantation.The ability of a patient/family member/caregiver to record seizures precisely into seizure diaries OR the ability of a patient/family member/caregiver to report seizures precisely in other ways.In cases with very high seizure frequency (several seizures per day), it is acceptable to report only the days without any seizures.

Patients meeting any of the following criteria are excluded:

The indication and planning of resective brain surgery as a treatment option for drug-resistant epilepsy. If a patient clearly demonstrates refusal of resective surgery, the patient can be included in the study.The presence of psychogenic non-epileptic seizures which cannot be reliably distinguished from epileptic seizures by a patient/family member/caregiver.The presence of another condition that can resemble epileptic seizures and which cannot be reliably distinguished from epileptic seizures by a patient/family member/caregiver.Metabolic condition or other diseases, in which an increase of seizure frequency can be expected.The inability of a patient to make regular visits.Life expectancy shorter than 2 years.

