The patients will be evaluated 1 and 2 years after the start of VNS therapy. The patient will be requested to report any changes in health history, including psychiatric disease, and specific requests will be focused on changes in medication (ASM and other drugs), VNS parameters settings, and seizures. The patients will be asked whether unexpected events influenced their clinical response. If these unexpected events are regarded as “clinically highly important” (such as non-compliance or other newly-diagnosed disease worsening epilepsy), the patient can be excluded based on clinical decision. The data on seizure frequency will be collected by reviewing the patient's diary. The reported seizure frequency will be compared with pre-implantation seizure frequency, and real-life response will be calculated in terms of real-life responders (seizure reduction ≥50%) or real-life non-responder (seizure reduction <50%). The patients will fill in a questionnaire focusing on the quality of life. If the patient does not tolerate at least the minimal VNS settings (0.75 mA) because of serious adverse events, they will be excluded from further analysis (the patient's data will be reported separately). The patients included in our study will be managed according to the best clinical praxis, i.e., the change of ASM and VNS parameters will be done based on the clinicians' decision to reflect the real-life response.

The information collected in Assessments 1 and 2, including real-life response to VNS, will be labeled with the patient's unique code and sent to the coordinating center, where it will be compared with the patient's predicted response.

At the end of Assessment 2, patients will be asked if they are interested in the predicted response to VNS. If the answer is yes, the study physician will contact the coordinating center, where the predicted response for a given patient will be conveyed. The patient will be informed about the predicted response by telephone or during a regular visit (not a part of the study protocol, described below).

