### Outcomes

The primary outcome of the study is the accuracy of the statistical model for prediction of response to VNS therapy in drug-resistant epilepsy, expressed as a percentage of correct predictions (responders vs. non-responders), evaluated after 2 years.

The secondary outcomes of the study are the quantification of differences in EEG power spectra (Relative Mean Power, %) between real-life responders and real-life non-responders to VNS therapy in drug-resistant epilepsy and the prediction of patients' response to VNS therapy in terms of responders, expressed as sensitivity of the model, and non-responders expressed as specificity of the model. If possible, these data can be used for further improvement of the statistic model.

The study is concerned with the verification of the real-life validity of our statistical classifier for the prediction of VNS response based on pre-implantation EEG data. The patients will be classified based on their predicted response as predicted responders (≥50% seizure reduction) and predicted non-responders (<50% seizure reduction). In Assessments 1 and 2, respectively, the patients' real-life response will be determined: real-life responders (≥50% seizure reduction) vs. real-life non-responder (<50% seizure-reduction). The predicted and real-life responses will be statistically compared in terms of accuracy, sensitivity, and specificity.

The individual patients' groups (predicted responders vs. predicted non-responders, real-life responders vs. real-life non-responders) will be compared based on their demographic data, health history, ASM, and VNS parameters. A suitable statistical test will be chosen concerning the characteristics of the data (Pearson's Chi-squared test for categorical variables, and Wilcoxon-Mann-Whitney test for continuous variables).

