### Sample Size

The sample size was estimated for the primary endpoint, which was defined as the accuracy of the statistical model for prediction of response to VNS therapy in terms of responders and non-responders in drug-resistant epilepsy. During the verification of the validity on the independent dataset, the model was able to predict the response to VNS with 86% accuracy. The minimal clinically significant accuracy was set to 70%. The sample size is estimated for the following hypothesis:

Hypothesis H0: *p* = 0.7 vs. Hypothesis H1: *p-value* > 0.7.

At the level of significance α = 0.05 and with a power of 90%, the number of patients needed for the analysis of the primary endpoint is 57. Assuming a drop-out rate of 50%, a total number of 114 patients should be enrolled.

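### Patients with several seizures a day may report only seizure-free days, but the reference label for model accuracy is a 50% cut in seizure frequency, which such data do not measure

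*Protocol article*

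**What the plan says.** Under Eligibility Criteria, after asking that seizures be recorded or reported precisely, the protocol article adds: "In cases with very high seizure frequency (several seizures per day), it is acceptable to report only the days without any seizures".

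The outcome is defined on a different scale. Trial Design says: "The real-life outcome will be measured by the percent of seizure reduction". The follow-up text under Protocol for EEG Recording says: "The reported seizure frequency will be compared with pre-implantation seizure frequency". It then sorts patients into "real-life responders (seizure reduction ≥50%) or real-life non-responder (seizure reduction <50" per cent). Outcomes makes agreement with that label the primary outcome, "expressed as a percentage of correct predictions (responders vs. non-responders), evaluated after 2 years". Statistical Methods derives sensitivity and specificity from the same label.

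No section gives a separate responder definition, or a conversion, for patients who report only seizure-free days. The Discussion concedes that diaries can be wrong through amnesia or conscious bias, but does not mention this reporting option.

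**The concern.** The model is judged against a reference label, so an error in the label counts as an error of the model. A record of seizure-free days says whether a day had any seizure, not how many. A patient who goes from 10 to 4 seizures a day has a 60% reduction but almost no seizure-free days before or after. The same 50% cut would therefore be applied to two measures that are not equivalent, in a subgroup defined by baseline frequency.

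This is more than a detail left for later. An analysis plan can choose a rule for seizure days, but it cannot recover counts that were never recorded. At stake are the primary accuracy estimate, at least one of the two secondary measures, and the power of the test against 70%.

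**Working it through.** **Inputs from the article.** Null accuracy 0.70, expected accuracy 0.86, α = 0.05, power 90%, 57 analysed and 114 enrolled (Sample Size). Sensitivity 83% and specificity 90% in the earlier validation, and about 50% responders at 1 year (Background and Rationale).

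**Assumptions, not in the article.** Daily rates of 2, 4 and 10 seizures; Poisson daily counts; 5, 10 or 20% of patients reporting only seizure-free days.

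**1. The plan's own figure.** The alternative is one-sided ("Hypothesis H1: *p-value* > 0.7"). The one-sample formula gives n = [(1.645·√(0.70·0.30) + 1.282·√(0.86·0.14)) / 0.16]² = 56.1, rounded up to 57; 57/0.5 = 114. Both stated figures reproduce. The exact binomial test at n = 57 needs at least 46 correct: α = 0.0486, power 0.906 at 86%.

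**2. What a true halving looks like in seizure days.** Share of days with a seizure = 1 − exp(−m), where m is the mean daily count. From 4 to 2 a day it goes from 0.982 to 0.865, a fall of 11.9%. Seizure-free days go from 0.5 to 4.1 per 30 days.

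| Baseline per day | Fall in seizure days after a true 50% reduction | True reduction needed to halve seizure days |
|---|---|---|
| 2 | 26.9% | 71.7% |
| 4 | 11.9% | 83.1% |
| 10 | 0.7% | 93.1% |

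The last column is 1 + ln(1 − d/2)/m, with d = 1 − exp(−m). For 10 to 4 a day, seizure-free days go from about 0 to 0.5 per 30 days and seizure days fall by 1.8%.

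Clustered counts (negative binomial, dispersion 0.3 to 3, baselines of 2 to 10 a day) give the same pattern: a true 50% reduction shows as 4–26%, and 73–92% is needed to halve seizure days.

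**3. The other reading.** If growth in seizure-free days is used, a true reduction of only 20% multiplies them by exp(0.2·m): 1.49 at 2 a day and 2.23 at 4 a day. A small improvement can then look large.

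**4. Worst case for the endpoints under the seizure-day reading.** Let f be the share of patients affected, and suppose all true responders among them are labelled non-responders. The starting accuracy is 0.5·0.83 + 0.5·0.90 = 0.865.

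- Accuracy = (1 − f)·0.865 + f·(0.5·0.17 + 0.5·0.90)
- Specificity = (0.45 + 0.5·f·0.17) / (0.5 + 0.5·f)
- Sensitivity = 0.5·(1 − f)·0.83 / [0.5·(1 − f)] = 0.83

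| f | Accuracy | Specificity | Sensitivity | Exact power, n = 57 |
|---|---|---|---|---|
| 0 | 86.5% | 90.0% | 83% | 0.92 |
| 5% | 84.9% | 86.5% | 83% | 0.85 |
| 10% | 83.2% | 83.4% | 83% | 0.76 |
| 20% | 79.9% | 77.8% | 83% | 0.52 |

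Starting from the article's rounded 86% instead, power goes from 0.91 to 0.83, 0.73 and 0.48.

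**The case against.** A reader might infer that these diaries can never show a 50% reduction, and that true responders are therefore known to be recorded as non-responders. The article does not support that.

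- **Direction.** One-way error needs a rule that reduction is computed on days with seizures. The article states no such rule, and the other obvious reading can reverse the error.
- **Absoluteness.** True reductions above the 72–93% thresholds do register, and a reduction that comes as whole seizure-free days registers in full.
- **Sensitivity.** It might seem to be the measure harmed. In the quantified scenario it is unchanged, because relabelled patients leave the responder group whatever their prediction. Specificity falls, because they join the non-responder denominator.

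Other points also carry weight. The option is permissive: the same list accepts reliable frequency information and precise reporting by other means, so a site may still hold counts or estimates for these patients. Relabelling every true responder in the subgroup overstates the loss, since large reductions stay correctly labelled. Even at a 20% share, expected accuracy remains above the 70% null. A conversion rule could also sit in a fuller protocol or an analysis plan.

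These points limit the direction and size of the problem but do not remove it. Where a site uses the option and holds nothing else, the percent reduction in seizure frequency cannot be calculated, and no later rule restores it.

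**Conclusion.** The concern holds in this form: the permitted seizure-free-day record and the 50% seizure-reduction label are on different scales, and the article does not reconcile them. For patients using the option, the reference label can be wrong in a direction that depends on an unstated rule.

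The accuracy, specificity and power losses shown for each assumed share are upper bounds. They rest on the seizure-day reading, relabelling of all true responders in the subgroup, 50% responders, and the earlier sensitivity and specificity. On those terms, a 5% share is already enough to take power below the planned 90%. The real share is not given, so the actual effect could be small. The change should be made because the flaw sits in the reference standard for the primary outcome and is cheap to prevent before data collection.

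**What to change.** Reconcile the reporting option with the 50% definition in the protocol:

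1. Patients with several seizures a day keep the seizure-free-day record and also count all seizures over the same fixed short window (for example 7 consecutive days) at baseline and before each of the two assessments. Percent reduction is computed from those counts.
2. Where counts are unavailable, classify by a seizure-day rule stated in advance, and report primary accuracy with and without these patients.
3. Report how many patients were classified by each route.

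The cost is a few sentences of protocol text and a short counting period per assessment for these patients. The downsides are slight caregiver burden, a noisier estimate than one from a longer record, and a few patients set aside in the sensitivity analysis. That last cost is not negligible where centres implant only 5–10 adults a year, which is why the counting window comes first and setting patients aside is confined to the sensitivity analysis. The planned 57 and 114 do not change.

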### Who Will Take Informed Consent?

The study protocol including the informed consent will be reviewed and approved by the Institutional Review Board at each of the sites. A trained study investigator will describe the study to patients or to authorized surrogates if applicable. Patients will also receive information sheets. The study investigator will discuss the study with patients based on the information provided in the information sheets. The study investigator will obtain the written informed consent from patients willing to participate in the trial. In the case of patients who are unable to give consent because of a medical condition, their ability to participate in the study will be assessed by a medical council consisting of at least one independent physician, who is informed about the study details, and one study investigator.

